### Power calculation

In calculating power, we use one-sided confidence intervals because previous studies have indicated CAMS to be superior to TAU [18, 23–25]. We use the following assumptions: (1) the main outcome variable BSSI-C score after treatment — which is scored on a 0–38 point scale — has a standard deviation of 7 points [27]; (2) there are equal sample sizes in the experimental and control groups; (3) a four-point difference in BSSI-C scores at follow-up will represent a meaningful clinical difference between CAMS and TAU; and (4) the alpha level is 0.05. Based on these assumptions, 82 % power will be achieved by including 80 participants in the trial, who will be randomized to CAMS or TAU. Assuming a 20 % drop-out rate, our desired sample size is 100 participants at inclusion.

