There is fairly robust and replicated evidence that CAMS is superior to other approaches for suicidal ideation and suicidal cognition [17, 22]. The overall CAMS approach has received preliminary support in seven non-randomized outcome studies. These include various correlational studies that support the usefulness of the approach in both outpatient and inpatient settings [23–25]. To date, well-powered randomized controlled trials are limited, but one small RCT conducted by Comtois and colleagues showed CAMS to be superior to TAU in terms of reduced suicidal ideation and symptom severity and increased hope, retention, and superior patient satisfaction [18]. A new Danish superiority RCT compared treatment conditions for borderline personality disorder with self-harm and suicidal behavior [26]. In this somewhat underpowered RCT, the investigators found no significant difference between DBT and CAMS for self-harm and suicide attempts at 28 weeks following treatment, which was surprising, given the robust evidence of the effectiveness of DBT for self-harm and suicide attempt behaviors [16].

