### Ethics

The trial has been approved by the ethical committee of medical research, health region South East Norway (reference number 2014/465). Several ethical considerations must be discussed and handled when conducting research on a vulnerable patient group. First, there is no reason to believe that CAMS has a poorer effect than TAU, as evidence until now suggests otherwise. Moreover, we have no indication that some patient groups respond better or worse than others. It follows that the CAMS arm of the trial will offer equally effective or better treatment as compared to TAU. The main intention of the study is to evaluate whether CAMS is more effective than TAU. Indeed, the major problem in this field is that the treatments that are administered lack controlled research support. If our hypothesis is supported, our goal is to contribute to the use of CAMS for future patients in our own and other clinics. It is important to stress that all suicidal patients will receive treatment during the study, whether CAMS or TAU. We will not offer a control group of patients who receive no treatment or postponed treatment. Participation is voluntary, and the patients are informed of their ability to withdraw from the study at any time.

The patients attending the project are not offered any remuneration, such as payment or gifts, for their participation in the trial. Therefore, we expect little to no vicarious motives for attendance other than general openness, agreeability, and interest. However, as we experienced recruitment difficulties, we decided to offer a small token of appreciation (a bag of chocolates) worth 6 US dollars to the clinical units for each patient they recruited to the trial.

The trial has been preregistered in the Open Science Network, registration code DOI 10.17605/OSF.IO/JHRM2 and in ClinicalTrials.gov with the ID NCT02685943. We have committed to publishing any results from the study and consider any findings important information in our work towards improving health services for patients who are suicidal.

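### The sample size rests on one-sided 5% inference, justified only by earlier favourable studies; a two-sided 5% test with the same inputs has about 71–72% power, not 82%

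*Protocol article*

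**What the plan says.** The Power calculation section opens with the choice of sidedness and its reason: "In calculating power, we use one-sided confidence intervals because previous studies have indicated CAMS to be superior to TAU". Four references support that sentence. The other assumptions follow in the same paragraph:

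- the post-treatment BSSI-C score "has a standard deviation of 7 points";
- "there are equal sample sizes in the experimental and control groups";
- "a four-point difference in BSSI-C scores at follow-up will represent a meaningful clinical difference between CAMS and TAU";
- "the alpha level is 0.05".

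From these the article concludes that 82% "power will be achieved by including 80 participants in the trial, who will be randomized to CAMS or TAU". Allowing for 20% drop-out, it aims for 100 at inclusion.

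Three other sections bear on the reason given.

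- **The CAMS approach** describes the evidence. Three of the four references cited for one-sidedness appear there among correlational studies, and the fourth is a small randomised trial against TAU. The support from non-randomised studies is called preliminary, and the section says: "To date, well-powered randomized controlled trials are limited".
- **Ethics** argues that "there is no reason to believe that CAMS has a poorer effect than TAU".
- **Removal from the trial, safety monitoring, and acceptability** has the therapist end CAMS or TAU if the process is judged inadequate or damaging to the patient.

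**The concern.** A one-sided test at 5% is defensible when a result in the other direction is impossible, or would lead to the same action as no difference. Expecting benefit meets neither condition. The evidence relied on is, by the article's own description, mostly non-randomised and short of well-powered trials. The safety section treats harm as something that can happen and must be acted on.

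Two things are at stake. The first is the false-positive risk in favour of CAMS: one-sided 5% allows 5% in that direction, where a conventional two-sided 5% test allows 2.5%. The second is the planning figure. A reader who sees 82% power and an alpha of 0.05 may carry the 82% over to a two-sided analysis, where it does not apply. In addition, a one-sided superiority test cannot declare CAMS worse than TAU, whatever the data show.

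**Working it through.** **Inputs, all from Power calculation:** SD 7, difference 4, alpha 0.05, 80 participants in equal arms (40 per arm), unadjusted comparison of follow-up scores.

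**Standard error and standardised signal**

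- SE = 7 × √(2/40) = 1.565
- 4 / 1.565 = 2.556

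**Step 1: reproduce the stated figure (one-sided 5%)**

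- Normal approximation: Φ(2.556 − 1.645) = Φ(0.911) = 81.9%
- Noncentral t, 78 df: 81.3%

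Both agree with the stated 82%. The inflation also agrees: 80 / (1 − 0.20) = 100.

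**Step 2: same inputs, two-sided 5%**

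- Normal approximation: Φ(2.556 − 1.960) = Φ(0.596) = 72.4%
- Noncentral t, 78 df: 71.4%

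So 82% is reproduced only by the one-sided test. The chance of missing a true 4-point difference rises from about 18% to about 28%.

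**Step 3: what each test requires**

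| | One-sided 5% | Two-sided 5% |
|---|---|---|
| False-positive risk in favour of CAMS | 5% | 2.5% |
| Smallest significant observed difference (t) | 1.665 × 1.565 = 2.6 points | 1.991 × 1.565 = 3.1 points |
| Power for 4 points | 81–82% | 71–72% |

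The difference detectable with 80% power, two-sided, is (1.960 + 0.842) × 1.565 = 4.39 points (4.44 by t).

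**Step 4: the size that unadjusted two-sided 80% power would need**

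This takes 98 analysed (normal) to 100 (t). At 20% drop-out that is 98 / 0.80 = 123 to 100 / 0.80 = 125 recruited, against the planned 100.

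**Step 5: adjustment for baseline BSSI-C**

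Adjustment multiplies the SE by √(1 − r²), where r is the correlation between baseline and follow-up scores. The article gives no value, so r is an assumption here.

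| Assumed r | SE | Signal | Two-sided power (t to normal) |
|---|---|---|---|
| 0 | 1.565 | 2.556 | 71–72% |
| 0.3 | 1.565 × 0.954 = 1.493 | 2.679 | 75–76% |
| 0.5 | 1.565 × 0.866 = 1.356 | 2.951 | 83–84% |

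**The case against.** **The power figure contains no error.** The sidedness stands in the same paragraph as the 82%, with every input needed to check it. A reader might infer that the authors miscalculated. They did not: the figure is right for the test described.

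**The silence of the Statistical analysis section proves nothing.** That section names generalized linear regression by intention to treat and gives neither sidedness nor level. A reader might infer that the final test contradicts the power calculation. A full protocol or analysis plan that is not shown may settle the matter, so this is not counted. The point rests only on what Power calculation itself states.

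**A one-sided interval does limit harm.** A reader might infer that it puts no bound on how much worse CAMS could be. That is backwards. A one-sided interval for the benefit of CAMS has a lower limit, and a lower limit of −1 would mean CAMS is at most 1 point worse at that confidence level. What it leaves open is the upper limit of benefit. It remains true that the one-sided test cannot declare CAMS inferior.

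**The trial's question is directional.** It is a superiority trial whose declared purpose is to learn whether CAMS is better. The CAMS approach section also claims fairly robust, replicated evidence on suicidal ideation, the domain of the primary outcome. This is a fair reply, but superiority trials are routinely tested two-sided. The same section limits its own claim by calling the non-randomised support preliminary and large trials few. The underpowered comparison of CAMS with DBT is not used here against the justification, because it was not a comparison with TAU and Power calculation does not cite it.

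**Recovery through baseline adjustment is uncertain.** This stands. Entry requires a BSSI-C score of 13 or more, which narrows the baseline range and may lower r. At r = 0.3 power stays below 80%.

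**Conclusion.** The concern holds as a criticism of a disclosed design choice. Favourable earlier studies do not justify one-sided inference at 5%. The choice doubles the false-positive risk in favour of CAMS (5% against 2.5%) and rules out a finding of harm.

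The size is about 10 percentage points of power: 81–82% one-sided against 71–72% two-sided. This assumes SD 7, a 4-point difference, 40 evaluable patients per arm and no covariate adjustment. If all 100 recruited patients gave full data, two-sided power would be 81.5% by the normal approximation, but the article's own calculation assumes that 20% are lost.

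**What to change.** - Make the primary BSSI-C comparison a two-sided 5% test, reported with a 95% confidence interval, and fix this before outcomes are examined. The article says recruitment was still open and that data stay on paper until all follow-up interviews are complete.
- Restate the unadjusted power as about 71–72% for 4 points with 80 evaluable patients, and 80% for about 4.4 points.
- Remove earlier results as the reason for the sidedness.
- Adjust the primary comparison for baseline BSSI-C, which Table 1 shows is collected at T1. Present any adjusted power as conditional on an assumed correlation: about 75–76% at r = 0.3 and 83–84% at r = 0.5.

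The cost is wording and a less favourable stated power. No extra patients are needed, provided the sponsor accepts that two-sided power for 4 points may stay below 80% if the correlation is low. Securing 80% without relying on adjustment would mean recruiting about 123–125, which this fix does not require.

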### Procedures

#### Recruitment

Recruitment is a collaborative process between the research assistants and general clinicians. Clinicians and leaders in the clinics are informed about the project and encouraged to inform and invite eligible patients to participate. Furthermore, four research assistants monitor the patient flow by attending meetings where the general patient flow is handled and processed: morning meetings where newly admitted patients are discussed, intake meetings where referrals for treatment are processed, and other fora where patient referrals are discussed. When potential participants are identified by clinicians or research assistants, the clinician who conducts the first assessment with the patient informs the patient about the project and invites him or her to participate if suicidality is part of the current problem complex. A short invitation letter is compiled for this use. If the patient agrees, he or she will meet with a research assistant to receive detailed information about the project. If the clinician finds that the patient no longer struggles with suicidal-related problems, e.g., the referral letter was misleading, the patient is not invited to participate. Furthermore, if the clinician in the first assessment finds that the patient’s language acquisition requires the use of a translator, she/he will not invite the patient to participate. A close collaboration between the clinic and the research team is essential.

Interested patients will meet a project assistant who provides thorough and written information about the aim of the study, the study design, and procedures. Ethics, data collection and storage of information, confidentiality, and the possibility to withdraw from the project at any time are also covered in these meetings. All screening interviews with research assistants will be conducted at the clinical unit already familiar to the patient. If an informed consent is offered by the patient, the research assistant follows up with the inclusion screening interview BSSI-C. Eligible participants who are actively suicidal as indicated by a positive score on item SS104 or SS105 and who score 13 or more are accepted for inclusion. At this point the patient is informed whether he or she may be included, and the randomization procedure is performed. Following this, the remaining baseline measures are acquired (see Table 1). Those with scores below the BSSI threshold are excluded from the trial but will receive usual care within the clinic.

**Table 1 Tab1:** Measurements at follow-up

Measures	T1 baseline	T2: 3 weeks	T3: 6 months	T4: 12 months	Outcome (1–10 years)
Primary outcome measure					
Beck Scale for Suicide Ideation - Current (BSSI-C)	x		x	x	
Secondary outcome measures					
Suicide Attempt Self-Injury Count (SASIC)	x		x	x	
Outcome Questionnaire-45 (OQ-45)	x		x	x	
Norwegian Patient Registry data (specified below)					x
Potential moderators and descriptive measures					
MINI		x			
Structured Clinical Interview for ICD-10		x			
Treatment history interview - short form	x		x	x	
Generalized Self-Efficacy Scale (GSE)	x		x	x	
Working Alliance Inventory - Short Revised (WAI-SR Client)		x			
Alcohol/Drug Use Disorders Identification Tests (AUDIT and DUDIT)	x				

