#### Randomizing and treatment allocation

Allocation to treatment group will be performed using a stratified four-block randomization procedure with treatment unit as the stratification variable. The randomization will be concealed to the clinicians recruiting patients to the study and is carried out by an independent statistician at the Norwegian Institute of Public Health. After screening and randomizing, the study participants will be followed for one year and meet with a trained research assistant at four checkpoints: T1, T2, T3, T4 (see Fig. 1).

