#### Assessments and measurements

The test battery will be administered by four research assistants. Completion of the baseline and the first follow-up interview (T1, T2) will take approximately 50–70 minutes each. Follow-up screenings after 6 and 12 months each will take approximately 25–45 minutes. We will perform a screener crossover at T3 and T4 so that the research assistant who screens for follow-up is blinded for treatment condition. Treatment condition is not concealed or blinded for the patient or the clinician treating the patient.

The research assistants consist of experienced psychiatric research nurses and psychiatric research health workers and the first author (WR). All have been formally trained for conducting the diagnostic interviews, and one research nurse has previous experience with attending and screening in another research project. The diagnostic interview is conducted in the follow-up interview at T2, after inclusion. After conducting the clinical diagnostic interview, the research assistant discusses and clinically validates the diagnostic conclusion with the first author or with the experienced research nurse. Beyond this, a more formal reliability check on diagnosis will not be carried out. Data will be stored in paper form until all follow-up interviews are completed and then entered into digital form for statistical analysis.

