#### Secondary outcomes

The * Suicide Attempt Self-Injury Count (SASIC)* is a brief interview covering past self-inflicted injuries, categorizing them into suicide attempts and non-suicidal acts [28]. The tool also creates counts of self-inflicted injuries by method, medical risk severity, and lethality. It has a Lifetime form and a Recent form which covers the last 6 months. The Lifetime version will be provided at baseline and the Recent form will be administered at T3 and T4.

The *Outcome Questionnaire - 45 (OQ-45)* is a 45-item questionnaire designed to measure key areas of mental health functioning (symptoms, interpersonal problems, and social role functioning). It is a widely accepted tool for identifying, tracking, and measuring behavioral health treatment outcomes and will be the measure of symptom distress in this study. OQ-45 possesses good psychometric properties when used with adult psychiatric patients, and it was recently shown to have high reliability and concurrent validity in a Norwegian sample [29]. OQ-45 will be administered at baseline and after 6 and 12 months.

*Norwegian Patient Registry (NPR)* measures are taken from administrative data on patients*.* All patients admitted to a hospital in Norway are registered in NPR. Primary NPR measures will be suicide attempts, new hospital admissions to any health treatment, and discharge diagnoses entered for the readmissions. Secondary measures will be intoxication and death by any cause.

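### Every T1 measure except BSSI-C is taken after randomisation, with nothing stated to keep the arm unknown while OQ-45, GSE and the other baselines are collected

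*Protocol article*

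**What the plan says.** The Recruitment section sets out one sequence. After consent, "the research assistant follows up with the inclusion screening interview BSSI-C". If the threshold is met, "At this point the patient is informed whether he or she may be included, and the randomization procedure is performed". The text continues: "Following this, the remaining baseline measures are acquired (see Table 1"). The section on randomising and treatment allocation is consistent with this: "After screening and randomizing, the study participants will be followed for one year", and it lists T1 among the checkpoints that come after.

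On blinding, Assessments and measurements says: "Treatment condition is not concealed or blinded for the patient or the clinician treating the patient". For the research assistants it says: "We will perform a screener crossover at T3 and T4 so that the research assistant who screens for follow-up is blinded for treatment condition". Nothing equivalent is stated for T1.

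Two secondary outcomes have a T1 score. For OQ-45, "OQ-45 will be administered at baseline and after 6 and 12 months". For SASIC, "The Lifetime version will be provided at baseline and the Recent form will be administered at T3 and T4". GSE is given at baseline and at both later follow-ups; AUDIT and DUDIT are given at baseline only. The aims name self-efficacy at the outset and alcohol and substance abuse as moderators. The Statistical analysis section lists baseline psychological measures among the covariates for estimating moderator effects.

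**The concern.** A baseline is safe to use as a covariate or moderator because allocation cannot have influenced it. Timing normally guarantees that. Here the timing is reversed for everything except BSSI-C, and neither patient blinding nor a stated delay in disclosure takes its place.

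OQ-45 asks about current distress and functioning, and GSE about belief in one's own ability to cope. Learning that one will receive a new suicide-specific therapy, or usual care, could plausibly change either answer on the day. A GSE score that allocation may have moved no longer measures self-efficacy at the outset, which is the moderator the aims name. An OQ-45 baseline that has moved would pass the shift into any analysis that subtracts it or adjusts for it. If some patients stop the visit after hearing their arm, missing baselines could also differ between arms, although nothing in the article shows that this happens.

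**Working it through.** **1. Which measures follow randomisation.** Table 1 marks six instrument rows at T1: BSSI-C, SASIC, OQ-45, treatment history, GSE and AUDIT/DUDIT. Only BSSI-C is the screening interview. So 6 − 1 = 5 rows come after randomisation.

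**2. Who may know the arm at that point.**
- Patient: not blinded; time of disclosure not stated.
- Treating clinician: not blinded.
- Research assistant: blinding stated at T3 and T4 only.
- Concealment from recruiting clinicians protects the allocation itself. It does not protect answers given after it.

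**3. How exposed each measure is.** OQ-45 and GSE record present state and belief, so both feelings and reporting could move. Lifetime SASIC, AUDIT/DUDIT and treatment history ask mainly about past events or behaviour, so only reporting could move.

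**4. The plan's own figures.** Inputs from Power calculation: difference 4, SD 7, 40 per arm, one-sided alpha 0.05.
- SE = 7 × √(2/40) = 1.565
- 4/1.565 − 1.645 = 0.911, and Φ(0.911) = 0.819, against the stated 82 %
- 80/0.8 = 100, as stated

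Both figures reproduce. They concern BSSI-C, whose baseline precedes randomisation, so neither changes.

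**5. Bias if a post-randomisation baseline is used.** Suppose knowing the arm shifts the recorded baseline by x between arms and does not itself carry over to follow-up. With true effect δ and within-arm slope β of follow-up on baseline:
- follow-up scores alone: δ, no bias
- change score: δ − x, bias x in absolute size
- baseline-adjusted: δ − βx, bias βx in absolute size

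The article gives no SD or correlation for OQ-45, so only an illustration is possible. Assume equal SDs (β = ρ, the correlation), 40 per arm, δ = 0 and a shift d in SD units. Then bias = ρd, SE = √((2/40)(1 − ρ²)), k = ρd/SE, and two-sided type I error = Φ(−1.96 + k) + Φ(−1.96 − k). For ρ = 0.5 and d = 0.2: bias 0.10, SE 0.194, k = 0.516, error 8.1 %.

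| d (SD) | ρ = 0.3: bias, error | ρ = 0.5: bias, error | ρ = 0.7: bias, error |
|---|---|---|---|
| 0.1 | 0.03, 5.2 % | 0.05, 5.8 % | 0.07, 7.2 % |
| 0.2 | 0.06, 5.9 % | 0.10, 8.1 % | 0.14, 14.2 % |
| 0.3 | 0.09, 7.1 % | 0.15, 12.1 % | 0.21, 26.0 % |

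The nominal level is 5 %. Every d and ρ is assumed.

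**6. Moderator analysis.** Let Y = a + bT + cG + dTG (here d is the interaction), with recorded score G* = G + xT. Substituting gives Y = a + (b − cx − dx)T + cG* + dTG*. A uniform shift leaves the interaction slope d intact but moves the treatment effect read at any recorded score by (c + d)x. If the reaction depends on the patient's level, so that G* = (1 + x₁)G in the CAMS arm, the slope there becomes (c + d)/(1 + x₁). With no true moderation (d = 0), a spurious interaction of −c·x₁/(1 + x₁) appears.

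**The case against.** The strongest reply is that the article fixes the order but not the disclosure. It says randomisation is performed; it does not say the patient or the T1 assistant hears the result before the remaining measures. The allocation is produced by a statistician outside the clinic, and the flowchart that might show the timing is not available here. This stands. A reader might infer that the baselines have been contaminated; the document supports only that they could be, with no safeguard described.

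Second, the Statistical analysis section names baseline measures under moderator effects only. It specifies neither a change score nor adjustment for baseline OQ-45, and Power calculation frames the effect as a difference at follow-up. This also stands: the formulas in step 5 are conditional, and a comparison of follow-up scores alone escapes the problem.

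Third, it is tempting to treat all five rows alike or to say that the moderator tests lose their validity. Neither is supported. Age, gender and ethnicity cannot be moved by allocation. The past-behaviour measures are less exposed. Lifetime SASIC at T1 and the Recent form later give no like-for-like change, and the analysis section does not name SASIC. A uniform shift would leave a linear interaction slope unchanged.

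Finally, the abstract calls the trial observer-blinded. The only mechanism given for that is the T3/T4 crossover, so it does not reach T1.

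What remains is an order of procedures stated outright, with no reason given for it. This step of the inclusion decision needs only BSSI-C.

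**Conclusion.** The point holds as a possible route to bias in secondary and moderator analyses, and no further. The order is certain. Knowledge of the arm at T1 is possible but not stated.

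The firmest consequence is for moderation by GSE, because the aims depend on its being a pre-treatment level. Moderation by AUDIT/DUDIT carries a smaller risk, but those instruments are scored only once, so no other measurement could replace them. OQ-45 is affected only if its baseline enters the analysis.

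A reader might infer that the primary result is biased through its baseline; it is not, because BSSI-C is taken before randomisation. The size and direction of any shift are unknown. The table shows only what assumed shifts of 0.1 to 0.3 SD would do in an adjusted comparison, from negligible (5.2 %) to material (26.0 %) at a nominal 5 %.

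**What to change.** **Patients still to be recruited.** Once BSSI-C eligibility is confirmed, complete SASIC, OQ-45, treatment history, GSE, AUDIT and DUDIT, and only then request or disclose the allocation. This adds no instrument. The cost is that allocation comes later in a visit the article puts at 50–70 minutes. By the Trial status section, recruitment was still open.

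**Patients already enrolled.** Record where possible whether the T1 measures were taken before or after the arm was disclosed. Run a sensitivity analysis that does not use post-disclosure OQ-45 and GSE baselines as covariates, and report moderator results based on those scores as exploratory. This costs a retrospective check of visit records and one extra analysis. It shows how far the results depend on the affected scores but cannot recover pre-allocation values.

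**Text.** State when the patient and the T1 assistant learn the arm. If disclosure already follows T1, one sentence saying so would largely settle the point.
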